### Plans to promote participant retention and complete follow-up {18b}

The data for primary and secondary endpoints will be collected during CTO-PCI, and the risk of missing data is therefore small (5% max). If a patient withdraws prematurely from the study they will not be replaced, and reasons for patient withdrawal must be documented in the eCRF. For patients lost to follow-up, attempts to contact the patient must be made and documented in the patient’s eCRF.

### Data management {19}

Data management will be completed using good clinical practices. All data will be entered, and a manual review will be done to avoid data entry error. The data will be entered into a validated database. The main author will be responsible for data processing, in accordance with the sponsor data management procedures. Validation checks will be performed and documented to ensure accurate, consistent, and reliable data. Data identified as erroneous, or data that are missing, will be referred to the investigative site for resolution through data queries. Correction procedures will be tracked. The database will be locked once quality assurance procedures have been completed prior to statistical analysis.

For medical information, the following dictionaries will be used:The latest version at the time of study starts of the Medical Dictionary for Regulatory Activities for medical history and adverse events.The latest version at the time of study starts (and each subsequent update as they become available throughout the duration of the study) of the World Health Organization Drug Dictionary for prior and concomitant medications.

### Confidentiality {27}

In accordance with the legal provisions in force (Articles L.1121-3 and R5121.13 of the Public Health Code), persons having direct access to the source data will take all necessary precautions to ensure the confidentiality of information related to experimental drugs, research, persons included in the study and especially their personal identity and the research results. Those persons, as well as the investigators themselves, are subject to professional secrecy. Each enrolled patient will have a personal eCRF with a unique identifier, in which all data related to the study will be recorded. Data collection will be the responsibility of the clinical trial staff at the site under the supervision of the site investigator. The investigator is responsible for ensuring the accuracy, completeness, legibility, and timeliness of the data entry. All source documents should be completed in a neat, legible manner to ensure accurate interpretation of data. All information required for the protocol has to be entered in the eCRF, and the investigator has to provide justification in cases of missing data entries. During the biomedical research or at the end of it, the data collected on the persons who are suitable and transmitted to the main author by the investigators will be anonymised, using the unique identifier of the case report form, to hide their name, address, contact information and date of birth. The trial steering committee will ensure that each enrolled patient provided written informed consent for access and use of their anonymised data.

### Plans for collection, laboratory evaluation and storage of biological specimens for genetic or molecular analysis in this trial/future use {33}

Not applicable as no biological samples will be collected for future analysis.

## Statistical methods

### Statistical methods for primary and secondary outcomes {20a}

Continuous variables will be reported as means, standard deviations, medians, and ranges, whereas categorical variables will be reported as numbers and proportions. Missing data will be considered separately for the calculation of proportions. Shapiro–Wilk tests will be used to assess the normality of data distributions. For normally distributed data, differences between groups will be evaluated using two-tailed *t*-tests. For non-normal distributions, differences between groups will be evaluated using Mann–Whitney *U* tests and Kruskal–Wallis tests. Effect sizes of differences between continuous variables (e.g. TIMI flow, procedure time, etc.) will be expressed using Cohen’s d, which can be interpreted as negligible (d<0.01),very small (0.01≤d<0.2), small (0.2≤d<0.50), medium (0.5≤d<0.80), large (0.8≤d<1.20), very large (1.2≤d<2.0), or huge (d≥2.0). For categorical data, differences between groups will be evaluated using chi-squared tests. All confidence intervals will be presented two-sided with a confidence level of 95%. Denominators used to calculate ratios for the intention-to-treat analysis will be the number of patients allocated to each treatment arm irrespective if they received the allocated treatment. Denominators used in the per-protocol analysis will be the number of patients that received treatment as allocated at enrolment. Denominators used in the as-treated analysis will be the number of patients that received treatment irrespective if the treatment was allocated at enrolment. Differences in success rate (successful wire crossing in ≤60 min with TIMI flow 3 is restored and residual stenosis is <30%) will be expressed in terms of absolute risk (as well as relative risk) to determine if procedures by CCTA CTO-PCA are 20% more successful compared to procedures by conventional Angiography CTO-PCI. Likewise, differences in complications between the two procedures will be expressed using absolute (as well as relative risk). A *p* value <0.05 will be deemed statistically significant. All statistical analyses will be performed using the latest version of R (R Foundation for Statistical Computing, Vienna, Austria).

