### Eligibility criteria {10}

The authors will enrol 130 patients undergoing difficult CTO-PCI.

The inclusion criteria will be:Men and women aged 18 to 90 years with body mass index (BMI) ≤ 40 kg/m^2^;Coronary artery chronic total occlusion (TIMI flow 0 for > 3 months) associated with myocardial viability (intended like normokinetic/hypokinetic wall motion or instrumental data in favour of viability) associated with ≥ 2 Canadian Cardiovascular Society (CCS) angina or ≥ 2 New York Heart Association (NYHA) dyspnoea or documented ischemia or ejection fraction < 50%;Coronary angiography J-CTO score ≥ 2;Understanding of, and agreement to comply with the study procedures;Signature of informed consent form prior to any study-related procedures; andAffiliation to social security scheme.

The exclusion criteria will be:Coronary angiography J-CTO score of 0 or 1;Pregnancy or other protection by law;Very frequent irregular cardiac rhythm (arrythmia?/tachycardia?) > 100 beats/min;Concomitant pathologies that introduce additional risks, such as hemodynamic instability, anaemia < 9 g/dl, gastrointestinal bleeding, thrombocytopenia with < 50,000/mm^3^ platelets count or severe valvular disease; orCT-scan performed before inclusion into the study.

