### Outcomes {12}

The primary objective of this study is to compare rates of successful wire crossing in ≤60 min in complex CTO (J-CTO ≥2) among the CT group and angiography group. Wire crossing will be considered successful if TIMI flow 3 is restored and residual stenosis is <30%. TIMI flow and residual stenosis will be evaluated by a pool of two cardiologists who are not directly involved in the procedure, and who are blinded to group allocation. The TIMI flow scale is classified as Grade 0 to 3 (Table 1).

**Table 1 Tab1:** TIMI flow grades

Grade 0	No flow
Grade 1	penetration without perfusion in the distal part of the artery
Grade 2	partial perfusion, the iodine contrast goes across the obstruction and fills the distal part of the artery, but the flow and the clearance of the iodine contrast are perceptibly slower if compared to the other non-occluded segments/arteries
Grade 3	complete perfusion, anterograde flow into the distal part of the artery with rapid filling and clearance if compared to the other segments/arteries.

The secondary objectives of the study are to compare:Success rates at any timeTotal time of PCI (minutes)Time of wire crossingRate of PCI complications (Major Adverse Cardiac Events, MACE): death, coronary perforation with cardiac tamponade requiring pericardiocentesis, myocardial infarction (if elevation of troponin or creatine kinase associated with change in electrocardiogram), stroke, major bleeding with loss of haemoglobin > 3 g/dl.Radiation levels during PCI expressed as transferred kinetic energy (air Kerma, Gy), dose area product (DAP, mGycm^2^), and fluoroscopy time (minutes).Volume of iodine contrast medium administered during PCI (millilitres).Cost of the PCI (euros) CTTA (CT group) Angiography Preoperative assessment, as summarised in the material invoice of every procedure.

Renal adverse events will be assessed after diagnostic coronary angiography, CCTA (CT group only), and CTO-PCI. Clinically relevant findings (like contrast allergic reaction) will be reported as adverse events. Their relationship with the CT scan or CTO-PCI will be reported. Other symptoms, such as angina CCS class, dyspnea NYHA class, MACE and renal failure will be recorded. Biologic markers, such as troponin, creatine kinase, creatinine, clearance of creatinine, and haemoglobin, will be recorded after CTO-PCI.

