## Assignment of interventions: allocation

### Sequence generation {16a}

An unstratified randomisation sequence will be generated before the commencement of the study by a software algorithm (IWRS, ClinInfo SAS, Lyon, France) and to be used in assigning patients to the CT group (A) or angiography group (B) in a 1:1 ratio. The randomisation list will consist of fixed block sizes of 4, e.g. AABB–BAAB–BABA–ABBA.

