## Data collection and management

### Plans for assessment and collection of outcomes {18a}

The following datasets will be defined:Intention-to-treat (effect of assigning the treatment): This dataset will include all enrolled patients allocated to either the CT group or the angiography group, irrespective of whether they undergo CTO-PCI, cross-over between treatment arms, or have incomplete post-intervention data.Per Protocol (effect of receiving the treatment): This dataset will include enrolled patients allocated to either the CT group or the angiography group, who undergo CTO-PCI, remain in their allocated treatment arm, and have complete post-intervention data (TIMI flow and residual stenosis available after PCI).As-treated (effect of adherence to a treatment arm): This dataset will include enrolled patients allocated to either the CT group or the angiography group, who undergo CTO-PCI, irrespective of whether they cross-over between treatment arms, and who have complete post-intervention data (TIMI flow and residual stenosis available after PCI).

The following information will be included on the eCRF after enrolment and allocation:Patients’ characteristics: age (years), sex, weight (kg), height (cm), and pregnancy test.Risk factors: smoking status, diabetes, hyperlipidaemia, hypertension, cardiovascular disease family historySymptoms related to the pathology (angina, dyspnea)Clinical/instrumental data: ECG, angiographic ejection fraction (EF), regional wall motion, ischemia, viability.Laboratory data: Troponin, creatine kinase, creatinine, clearance of creatinine, haemoglobin.Anamnestic data: previous PCI, previous CTO-PCI attempt without success, previous bypass surgery.Relevant comorbidity (renal function disease, pulmonary disease, peripheral artery disease, others), arrhythmias, allergyCoronary anatomy based on coronary angiography and to calculate the J-CTO score for all the patients. For the CT group, coronary anatomy will be reassessed with the CCTA and in addition to the J-CTO Score based on the CCTA, the CT-RECTOR and calcium scores will be calculated.

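### Air kerma and dose area product are compared without adjustment for recorded baseline body size: valid tests, but a possible gain in precision is left unused

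*Protocol article*

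**What the plan says.** Section {20a} of the protocol article, which covers both primary and secondary outcomes, gives one rule for continuous variables. After a Shapiro–Wilk check, "For normally distributed data, differences between groups will be evaluated using two-tailed" t-tests; "For non-normal distributions, differences between groups will be evaluated using Mann–Whitney" U and Kruskal–Wallis tests. It names no covariate, and no regression or analysis of covariance appears elsewhere in the article. The only additional analysis, in {20b}, is a subgroup split at J-CTO 2 versus 3 or more.

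Outcomes {12} lists, as a secondary objective, "Radiation levels during PCI expressed as transferred kinetic energy (air Kerma, Gy), dose area product (DAP") and fluoroscopy time. The rule in {20a} therefore governs all three.

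Body size is available. The eCRF items in {18a} include "age (years), sex, weight (kg), height (cm), and pregnancy test". Eligibility {10} admits "Men and women aged 18 to 90 years with body mass index (BMI) ≤ 40 kg/m"², so BMI must be known before a patient is admitted, and Table 2 in {13} marks demographic data at enrolment, ahead of allocation. On allocation, {16a} says: "An unstratified randomisation sequence will be generated before the commencement of the study by a software algorithm".

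**The concern.** The X-ray output needed to form an image generally rises with the thickness of the patient. This is general physics and is not stated in the document. If it explains a material share of the between-patient variation in air kerma and dose area product, an unadjusted comparison carries that share as noise. The confidence interval is then wider than it need be and power is lower. Eligibility sets an upper BMI limit of 40 and no lower limit, so some spread in body size is to be expected, and the unstratified randomisation does nothing to balance it.

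What is at stake is the precision of one secondary comparison. Objectives {7} names radiation as something to compare, and the Background and Discussion name lower irradiation as a potential benefit of CCTA planning. The sample size in {14} rests on the primary endpoint alone, so nothing in the plan secures precision for radiation.

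**Working it through.** **Figure to reproduce.** There is none on this point. The article gives no standard deviation, target difference, power or precision for any radiation measure, and no correlation between body size and dose.

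**Inputs from the document.** 65 patients per arm randomised, and 56 per arm before the allowance for losses ({14}). Two-sided testing at 0.05 ({20a}).

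**Assumptions.** The within-arm correlation r between body size and the dose measure (log dose if skewed) is taken as 0.1 to 0.6. The standardised difference d is set at 0.5 for illustration. Neither is in the document.

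**Formulas.** Adjustment for a baseline covariate multiplies the residual variance by 1 − r² and the standard error by √(1 − r²). The equivalent unadjusted size is 65/(1 − r²) per arm. Power comes from the noncentral t with 128 degrees of freedom and noncentrality d·√(65/2)/√(1 − r²).

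**Unadjusted.** 0.5 × √32.5 = 2.85, which gives power of 80.8%.

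| r | 1 − r² | SE reduction | Equivalent n per arm | Power at d = 0.5 |
|---|---|---|---|---|
| 0 | 1.00 | – | 65 | 80.8% |
| 0.1 | 0.99 | 0.5% | 65.7 | 81.1% |
| 0.2 | 0.96 | 2.0% | 67.7 | 82.3% |
| 0.3 | 0.91 | 4.6% | 71.4 | 84.3% |
| 0.4 | 0.84 | 8.3% | 77.4 | 87.0% |
| 0.5 | 0.75 | 13.4% | 86.7 | 90.4% |
| 0.6 | 0.64 | 20.0% | 101.6 | 94.3% |

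**Cost of the covariate.** One extra parameter inflates the standard error by about √(128/127) = 1.004, or 0.4%. At r = 0.1 the net factor is 0.995 × 1.004 = 0.999, so the gain has all but vanished. At r = 0.2 it is 0.980 × 1.004 = 0.984, still a small gain.

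**If losses leave 56 per arm.** The same calculation at d = 0.5 gives 74.6% unadjusted, 76.3% at r = 0.2, 85.7% at r = 0.5 and 90.6% at r = 0.6.

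**What the table does not measure.** These figures isolate covariate adjustment. They say nothing about the effect of a log transformation, or about a log-scale model against the Mann–Whitney test.

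**The case against.** The strongest reply is that nothing here is wrong. Under 1:1 randomisation the unadjusted tests are valid and unbiased, and covariate models for secondary endpoints are often left to an analysis plan, which is not shown. The first part stands. The second stands only in part. Section {20a} is not silent: it names the test for these outcomes, and the point concerns that choice. A separate plan could still add an adjusted analysis.

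The size of the gain is also open, and this stands in full. The document does not link body size to dose. The one source of PCI dose variation it does name, in the Discussion, is longer procedures, and adjusting for body size does not remove that. The BMI limit of 40 also restricts the spread at the upper end.

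Three stronger readings are tempting and are not supported:

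- A reader might infer that a chance difference in body size between arms biases the dose comparison. It does not. The ordinary error rates and intervals already allow for chance imbalance, and adjustment would only sharpen the estimate.
- A reader might infer that precision is demonstrably being thrown away. The document cannot show that. At r of 0.2 or less the gain is immaterial.
- A reader might extend the point to all the radiation measures. Fluoroscopy time is a duration, and nothing in the document ties it to body size.

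**Conclusion.** The point holds as a minor efficiency improvement for air kerma and dose area product. The planned analysis is valid but does not use a baseline variable that is already collected and plausibly related to dose. The benefit ranges from negligible (standard error down 0.5% at r = 0.1 and 2% at r = 0.2) to useful (13% at r = 0.5 and 20% at r = 0.6). At 65 per arm and d = 0.5, power moves from about 81% to at most about 94%. Both r and d are assumptions, so no particular loss can be attributed to the plan. The primary endpoint is unaffected. The recommendation rests on the asymmetry: the cost is about 0.4% of the standard error per covariate, whatever r turns out to be.

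**What to change.** In {20a}, prespecify before database lock that air kerma and dose area product, and not fluoroscopy time, are each analysed with a linear model containing arm and baseline BMI (or weight). Use the log scale if the data are skewed. Report the adjusted difference, or the ratio of geometric means on the log scale, with a two-sided 95% confidence interval. Keep the planned t or Mann–Whitney test as a supporting result. State that the covariate is the value taken at enrolment, because {18a} describes eCRF entry as following allocation whereas Table 2 places demographic data at enrolment.

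The cost is a sentence or two of analysis text, one extra model per endpoint and one or two degrees of freedom out of 128. It needs no new data and no additional patients.

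### A normality pretest chooses the test for every continuous outcome, so skewed cost would probably go to a rank test that does not compare mean cost

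*Protocol article*

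**What the plan says.** Statistical methods for primary and secondary outcomes {20a} sets one route for all continuous outcomes. First, "Shapiro–Wilk tests will be used to assess the normality of data distributions". Then "For normally distributed data, differences between groups will be evaluated using two-tailed" t-tests, whereas "For non-normal distributions, differences between groups will be evaluated using" Mann–Whitney and Kruskal–Wallis tests. No outcome is exempted and cost has no method of its own. On estimation the section says "Effect sizes of differences between continuous variables (e.g. TIMI flow, procedure time, etc.) will be expressed using Cohen’s d", with no exception when the p value comes from ranks. On description it says "Continuous variables will be reported as means, standard deviations, medians, and ranges".

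Outcomes {12} lists cost in euros among the secondary outcomes to be compared. The entry names the PCI, the CT (for the CT group), the angiography and the preoperative assessment, "as summarised in the material invoice of every procedure". Background and rationale {6a} expects CCTA planning to reduce costs. Intervention description {11a} gives every CT-group patient an additional scan. The Discussion says that procedures running beyond 60 minutes cost more because they use more material.

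**The concern.** Whether means or ranks are compared is decided by the data, outcome by outcome. When the rank branch is taken, the p value refers to ranks while the reported effect size refers to means.

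For cost this matters in substance. Whether a strategy reduces costs is a question about total cost, and so about the arithmetic mean. A rank test asks instead whether a patient in one arm tends to cost more than a patient in the other. The protocol's own account suggests how the two can part. The scan adds a similar amount to every CT patient, while the saving comes from having fewer long, expensive procedures. Ranks give weight to the small shift that affects everyone and little weight to the size of the upper-tail saving. The trial could then miss a real mean saving or, in some settings, report CT as significantly dearer when its mean cost is equal or lower.

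**Working it through.** **There is no plan figure to reproduce.** The protocol states no cost mean or SD, so every euro amount below is an assumption.

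**Inputs from the protocol.** 65 patients per arm and planned success within 60 minutes of 70% vs 90% (Sample size {14}); significance at p < 0.05 (Statistical methods {20a}).

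**Assumed inputs.**
- Base cost is lognormal with mean 3000 euros and coefficient of variation (CV) 15%, 25% or 35%.
- A long procedure costs double.
- The share of long procedures is the complement of planned success: 30% (angiography) vs 10% (CT).
- A fixed CCTA cost *c* is added to every CT patient.

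**True means.**
- Angiography: 0.70 × 3000 + 0.30 × 6000 = 2100 + 1800 = 3900 euros.
- CT: 0.90 × 3000 + 0.10 × 6000 + *c* = 2700 + 600 + *c* = 3300 + *c* euros.
- CT minus angiography: *c* − 600 euros.

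**Step 1: which branch is taken.** In this model Shapiro–Wilk rejected in 100% of simulated trials. With plain lognormal costs at 65 per arm, it rejected in at least one arm in 88% of trials at CV 30%, 99.9% at CV 50%, and 100% at CV 80% or more.

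**Step 2: what each test then concludes** (two-sided 0.05; at least 1500 simulated trials per setting, so a result near 20% has a standard error of √(0.2 × 0.8 / 1500) ≈ 1 point). Where three values are listed, they are for CV 15%, 25% and 35%.

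| CCTA cost counted | True mean difference (CT − angiography) | Mann–Whitney: CT cheaper | Mann–Whitney: CT dearer | Welch |
|---|---|---|---|---|
| 0 | −600 | 40–53% | at most 0.1% | cheaper in 50–76% |
| 200 | −400 | 6–13% | about 1% or less | cheaper in 25–41% |
| 400 | −200 | 0.2% at CV 15% | 18%, 5%, 4% | at CV 15%: cheaper in about 14%, dearer in 0.2% |
| 600 | 0 | at most 0.5% | 61%, 22%, 14% | rejects in about 5%, either direction |

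**Step 3: different assumptions.**
- Lognormal costs with equal true means of 5000 euros and unequal spread (CV 60% vs 30%, 80% vs 40%, 100% vs 40%, angiography first): Mann–Whitney rejects in 28%, 39% and 64% of trials, Welch in 5.2%, 5.8% and 6.3%.
- A mixture in which CT adds 300 euros to every case and costly long cases fall from 30% to 10%: mean cost is lower with CT (4641 vs 5022 euros) but median cost is higher (4370 vs 4280). Welch rejects in 24% of trials, Mann–Whitney in 6%.
- The same lognormal distribution in both arms: both tests reject in about 5%, so there is no problem.

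**The case against.** Four points deserve weight.

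**The target is inferred.** The protocol nowhere names mean cost as the quantity of interest, and it reports medians as well as means. This stands as a limit. The inference rests on the expected cost reduction, the comparison in euros and the choice of a mean-based effect size.

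**It is unclear whether CCTA cost is counted.** The Abstract speaks only of the cost of the PCI. The entry in Outcomes {12} runs its items together, and it could mean either a total or separate items. If the PCI invoice is compared alone, the first row of the table applies: both tests point the same way and the rank test only loses power. This stands too, and it is a reason to clarify the entry.

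**The wrong-direction result is confined to certain settings.** A reader might infer from the 61% that the trial is likely to call CT dearer wrongly. The protocol does not support that. The figure needs a scan cost that exactly cancels the saving and the least variable costs tried. At 400 euros with CV 25–35% the risk is 4–5%, and at 200 euros or less it is about 1% or lower. A significant rank result opposite to the observed mean difference occurred in 15% of trials at 600 euros and CV 15%, but in well under 1% at CV 25% or 35%.

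**A discrepancy would be visible, and details may sit in an analysis plan.** Means, SDs and Cohen's d would indeed be shown beside the p value. Significance would still be declared by the stated rule, which this article fixes and does not leave open.

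**Conclusion.** The point holds in limited form. The rule as written probably sends cost to a rank test, which does not answer whether CCTA lowers mean cost. The more robust consequence is lost power: 6–13% against 25–41% when CT is truly 400 euros cheaper with a 200-euro scan, and 40–53% against 50–76% when the scan is not counted. A false finding that CT is dearer is possible, but only if the scan cost is included and is large relative to the saving.

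These sizes rest on assumed costs, on long cases costing double, and on carrying the planned 30% vs 10% into cost. They illustrate the mechanism and do not predict this trial's result. For times, radiation and contrast volume, a rank p value beside Cohen's d is a mismatch worth tidying. No error rate was shown for those outcomes, and the choice of method there is largely a matter of preference. Cost is a secondary outcome; the binary primary endpoint, its chi-squared test and its risk measures are untouched.

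**What to change.** In Statistical methods {20a}, or in the analysis plan with a matching amendment:

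- Remove the Shapiro–Wilk selection step for cost. State that the comparison is the difference in arithmetic mean cost between arms, with a Welch or bootstrap 95% CI.
- In Outcomes {12}, state whether the CCTA cost is part of the compared cost or is itemised separately.
- For the other continuous outcomes, name the test in advance and report an estimate that matches it, for example Mann–Whitney with a Hodges–Lehmann shift, or a t-test on the log scale. Keep Cohen's d only where means are compared.

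The cost is a few sentences and a few lines of R, with no new data and no change to sample size or conduct. The wording should be settled before any comparison by arm is seen.

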The primary endpoint, that is the success rate of difficult CTO-PCI in ≤60 min wire manipulation, will be assessed for each of the three datasets, i.e. intention-to-treat, per-protocol and as-treated, after the CTO-PCI (D0, Table 2). The TIMI flow and residual stenosis after the procedure will be recorded for each of the three datasets, i.e. intention-to-treat, per-protocol and as-treated, and will be assessed at immediate follow-up (D0 + 2 to 4 days) and final follow-up (D0 + 180 days). Laboratory parameters will be recorded for each of the three datasets, i.e. intention-to-treat, per-protocol and as-treated, and will be assessed at immediate follow-up (D0 + 2 to 4 days). The success rate of the complex CTO-PCI between both groups will be calculated for each of the three datasets, i.e. intention-to-treat, per-protocol and as-treated, at immediate follow-up CTO-PCI (D0 + 2 to 4 days) and final follow-up (D0 + 180 days). For all three datasets, i.e. Intention-to-treat, Per-protocol and As-treated, all adverse events will be recorded according to the corresponding system organ class (SOC) and preferred term (PT) using the MedDRA terminology. Creatinine levels after the CTO-PCI, summarising the renal adverse events, will be described in both groups. Symptoms (angina CCS class/dyspnea NYHA class), MACE, and renal failure will be evaluated at the CTO-PCI visit and end of study visit.

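### TIMI flow is a four-grade ordinal scale, but the analysis section lists it as continuous and gives it Cohen's d, which can disagree with the proportion reaching TIMI 3

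*Protocol article*

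**What the plan says.** Three parts of the protocol bear on this.

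- **Outcomes {12}** defines the scale: "The TIMI flow scale is classified as Grade 0 to 3 (Table 1"). Table 1 describes each grade in words, from no flow at grade 0 to full flow at grade 3. Grade 2 is "partial perfusion, the iodine contrast goes across the obstruction and fills the distal part of the artery", but more slowly than elsewhere. The success rule uses one cut on this scale: "Wire crossing will be considered successful if TIMI flow 3 is restored and residual stenosis is <30"%.
- **Statistical methods for primary and secondary outcomes {20a}** sets two kinds of summary: "Continuous variables will be reported as means, standard deviations, medians, and ranges, whereas categorical variables will be reported as numbers and proportions". It then states: "Effect sizes of differences between continuous variables (e.g. TIMI flow, procedure time, etc.) will be expressed using" Cohen's d, with labels running from negligible (below 0.01) through small (0.2 to below 0.50) and medium (0.5 to below 0.80) to huge. TIMI flow is the first example named. For the group test: "For non-normal distributions, differences between groups will be evaluated using Mann–Whitney *U* tests and Kruskal–Wallis tests". Success is handled separately; differences in it "will be expressed in terms of absolute risk (as well as relative risk").
- **Plans for assessment and collection of outcomes {18a}** adds: "The TIMI flow and residual stenosis after the procedure will be recorded for each of the three datasets", with assessment at immediate and final follow-up.

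Nothing elsewhere in the protocol moves TIMI flow to the categorical variables.

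**The concern.** Table 1 orders the grades but does not say that the step from 0 to 1 equals the step from 2 to 3. A mean, an SD and a d computed on the codes 0 to 3 assume exactly that. The outcome should also be bunched: patients enter with an occluded artery, and the design expects most to succeed. A mean and SD describe such a distribution poorly.

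What is at stake is how the flow result reads in the report. A labelled effect on TIMI flow could stand beside equal TIMI 3 proportions, or a negligible one beside clearly different proportions. The reader could not tell which to believe without the grade table, and classing TIMI flow as continuous removes that table.

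**Working it through.** The protocol states no figure for TIMI flow, so there is none to reproduce. The sample size enters only through the 65 patients per arm. **The grade mixes below are assumptions.**

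**Formula.** d = (mean₁ − mean₂) / pooled SD. With equal arms, pooled SD = √[(var₁ + var₂)/2]. If a proportion p is at grade 3 and the rest lie at a distance k below it, the mean is 3 − k(1 − p) and the variance is k²p(1 − p).

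**1. Equal TIMI 3 proportions, different failure grades.** Take 80% at grade 3 in both arms, with failures at grade 2 (k = 1) in one and grade 0 (k = 3) in the other.
- Means: 3 − 0.2 = 2.8 and 3 − 0.6 = 2.4; difference 0.40.
- Variances: 0.16 and 9 × 0.16 = 1.44; pooled SD = √0.80 = 0.894.
- d = 0.40/0.894 = 0.447, labelled *small*. With 52/65 per arm and sample SDs it is 0.44.

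The same contrast gives 0.57 (*medium*) at 46/65 per arm and 0.31 at 58/65 per arm. A milder contrast at 46/65 per arm, with failures at grades 0/1/2 numbering 4/2/13 against 13/2/4, gives 0.27.

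**2. Different TIMI 3 proportions, no d.** Take 58/65 at grade 3 with 7 failures at grade 0, against 44/65 at grade 3 with 21 failures at grade 2.
- Means: (58 × 3)/65 = 174/65 = 2.677 and (44 × 3 + 21 × 2)/65 = 174/65 = 2.677.
- d = 0, labelled *negligible*.
- The TIMI 3 proportions are 89.2% and 67.7%, a difference of 14/65 = 21.5 points; chi-squared p = 0.003.

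**3. Dependence on spacing.** In case 1, let failures lie at distances x and y below grade 3, with x < y. Then d = 0.2(y − x)/√[0.08(x² + y²)], which depends only on the ratio x/y. The coding 0 to 3 fixes that ratio at 1/3 and gives 0.447. Keeping only the order, the ratio can lie anywhere between 0 and 1, and d then lies between 0.2/√0.08 = 0.71 and 0. Table 1 does not supply the ratio.

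**4. The rank-based alternative.** Mann–Whitney uses order only. It gives p = 0.57 in case 1 at 52/65 per arm, p = 0.29 at 46/65 per arm (beside d = 0.57), and p = 0.013 in case 2. The matching effect measure is the probability of superiority, with ties counted half:
- Case 1: 0.8 × 0.2 + 0.2 × 0.2 + ½(0.8 × 0.8) = 0.16 + 0.04 + 0.32 = 0.52.
- Case 2: (58 × 21)/65² + ½(58 × 44)/65² = 0.288 + 0.302 = 0.59.

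The ordinal measure is near the null (0.5) in case 1 and away from it in case 2, the reverse of d.

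**The case against.** The strongest reply is that little depends on this. Success is analysed as a proportion with absolute and relative risk. TIMI grade is not a listed secondary endpoint. Shapiro–Wilk rejects normality in every example (p < 10⁻¹¹), so the group test would be Mann–Whitney, which suits ordinal data. All of that stands and limits the weight of the point. It does not rescue the effect size, because Cohen's d is prescribed for continuous variables whichever test is used.

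Three stronger readings are tempting and are not supported.

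- *A reader might infer that d cannot distinguish a persistent occlusion from near-normal flow.* That holds only when failures sit at the same grade in both arms. With 90% against 70% at grade 3, d = 0.2/√[(0.09 + 0.21)/2] = 0.516 whether all failures are at grade 0, 1 or 2. Spacing is then irrelevant too, and a rank test or the TIMI 3 risk difference is equally insensitive. When failure grades differ between arms, d does react, as case 1 shows. Moreover, 90% and 70% are the protocol's assumed success rates within 60 minutes. They are not TIMI 3 rates, and the Discussion allows longer procedures to reach TIMI 3.
- *A reader might infer that any effect at equal TIMI 3 proportions is an error.* It is not. If one arm's failures are grade 2 and the other's grade 0, flow does differ, and an ordinal measure also moves (0.52 in case 1). The fair criticism is that the size of d comes from the coding.
- *A reader might infer that the primary result is at risk because TIMI 3 is part of it.* The primary analysis uses the dichotomy and never the mean grade.

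**Conclusion.** The point holds as a minor one. Naming TIMI flow as a continuous variable contradicts Table 1, and following the text gives an unsuitable mean, SD and d. Under the assumed mixes, d is 0.27 to 0.57 with equal TIMI 3 proportions and 0 with a 21.5-point difference. Most of these mixes put all of an arm's failures at a single grade, so they show what can happen, not what is likely; the 0.27 comes from the milder mix. The primary endpoint, the sample size and the rank-based test for non-normal data are unaffected.

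**What to change.** In the statistical methods section:

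- remove TIMI flow from the examples of continuous variables;
- report the number and proportion in each grade 0 to 3 by arm, with the risk difference and relative risk (95% CI) for TIMI 3;
- if the whole scale is compared, keep the Mann–Whitney test and pair it with an ordinal effect measure such as the probability of superiority;
- reserve Cohen's d for measured quantities such as procedure time.

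The cost is a short edit to that section. It needs no new data or patients. The counts and risk measures are already used elsewhere in the plan; only the ordinal effect measure is new.
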